### Pre-randomisation phase

Potential participants will be identified in specialised nodding syndrome outpatient clinics or community outreach centres. Screening, assent and informed consent procedures will be performed in the same clinics and the community outreach centres by study staff. The inclusion criteria will be patients with confirmed nodding syndrome as defined by the WHO [25] and aged 8 years or older. Females with a positive urinary HCG (pregnancy) test (tested if the participant has experienced menarche), those anticipated to migrate away from the study catchment area, those with known hypersensitivity to tetracyclines, and those with suspected high likelihood of non-compliance to the study drug or follow-up schedule will be excluded. Patients on phenobarbitone, carbamazepine, or phenytoin will first be weaned off and put on sodium valproate, the standard of care antiepileptic drug, before enrolment.

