### Inpatient assessment

After eligibility is confirmed and consent obtained, the subject will be hospitalised for 1–2 weeks in Kitgum General Hospital for baseline assessments. The patients’ treatment will be updated per standard of care protocols. The clinical assessment will include a review of the pregnancy, birth and developmental history, the past medical history, a description of the progressive development of the symptoms of nodding syndrome, and the burden and types of seizures. A detailed physical assessment will also be performed including a neurologic, psychiatric and cognitive examination. The Gross Motor Function Classification System (GMFCS) and the Modified Rankin Scale will be used to describe gross motor abilities. The Mini-International Neuropsychiatric Interview for Children and Adolescents (MINI-KID) [26] will be used to document psychiatric disorders and the disorders classified per the Diagnostic Statistical Manual (DSM)-V criteria; Intellectual Disability will be assessed using the Child and Adolescent Intellectual Disability Screening Questionnaire (CAIDS-Q) [27]; nutritional status will be assessed against WHO 2000 anthropometric standards; cognitive function will be assessed using the Cogstate - a computerised cognitive testing program [28], and the quality of life (QOL) will be assessed using the Quality of Life in Childhood Epilepsy (QOLCE) questionnaire [29].

All participants not on standard of care treatments will be initiated on therapy including sodium valproate for seizures, nutritional, physical and psychological therapy as appropriate. Patients receiving current standard of care treatment but with ongoing seizures will have their doses of sodium valproate optimised to 20-35 mg/kg/day.

Five-10mls of blood will be drawn for standard of care testing (full blood count, liver and renal function tests, and HIV). We will also obtain skin snips for *O.volvulus* microfilaria density (on microscopy and Real Time [RT] PCR) and *Wolbachia* load testing. Lumbar puncture will be performed and 3-4mls of cerebrospinal fluid obtained. Aliquots of plasma, serum and cerebrospinal fluid will be stored for baseline evaluation of study specific tests.

All will have a 30-min diagnostic electroencephalographic (EEG) recording. In addition, an overnight EEG will be obtained in a convenient sample of 45 participants selected by stratified random sampling to reflect the five clinical stages of nodding syndrome [30].

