### Randomisation, allocation and treatment initiation phase

Once all pre-randomisation assessments are complete, participants will be randomised to either doxycycline or placebo with a 1:1 allocation as per a computer-generated randomisation schedule stratified by skin snip test results in to four groups; A, B, C and D. The randomisation code and stratification will be prepared by an independent statistician at a data centre at Global Health Uganda. The study pharmacy assistant will email the independent data centre with the study ID and the microscopy results of the skin snip for *O.volvulus* and the data centre statistician will allocate the participant to the study arms*.*

Eligibility criteria for randomisation are fulfilment of the enrolment criteria and the dose of sodium valproate rationalised to at least 20 mg/kg/day (maximum 35 mg/kg/day) if the patient still experiences one or more tonic clonic seizures a month. Participants reported to be unable to swallow capsules, those already enrolled (or who will enrol) into another trial, and those who withdrew consent since enrolment, will be excluded from randomisation.

The intervention drugs (doxycycline capsules [Azudox®] and placebo) will be obtained from Kampala Pharmaceutical Industries, Uganda. The active drug and the placebo will be labelled with the study code by Kampala Pharmaceutical Industries in collaboration with the independent statistician. Each Azudox capsule contains doxycycline hyclate equivalent to 100 mg of doxycycline base. In the treatment of *Onchocerca volvulus,* doxycycline is given in doses of 100-200 mg/day for 4–6 weeks [31]. We chose the lower dose of 100 mg/day since most participants will be adolescents many of who will also have wasting. With an average weight of 33 kg, we anticipate this dose will translate to ~ 3 mg/kg/day. The two interventions will be identical in the number of capsules (one) per day and timing. The drug administration procedures will also be identical. Both the caretakers and investigators will be blinded. However, in the event of medical emergency un-blinding of an individual participant to the PI or safety monitoring teams may be conducted. Otherwise, all treatment allocations will only be disclosed after the data is locked and a statistical analysis plan is in place.

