#### Secondary efficacy outcomes

Key secondary efficacy measures at 24 months will include:Mean change in serum levels or titres of antibodies to HNPs or leiomodin and serum levels or titres of inflammatory markers.Mean change in dermal microfilaria density on real time PCR at 24 months.The proportions of patients achieving seizure freedom (≥1 month without head nodding or convulsive seizures), mean change in Cogstate scores, the proportions of patients with inter ictal epileptiform discharges on diagnostic EEG, proportion of participants with Gross Motor Function Classification System (GMFCS) scores 3–5; and the proportion of participants with mental health disorders on the MINI-KID and intellectual disability on the CAIDS-Q and the proportion of participants with improved Quality of Life.Others will be mean changes in weight-for-age, height-for-age (stunting), and height-for-weight (wasting) Z-scores and proportions of participants with wasting and stunting (Z-scores <− 3 SD)Incidence rate of non-nodding syndrome sick clinic visits and all cause sick clinic visits; incidence rate of all-cause hospital admissions and all-cause mortality

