### Statistical analysis

Analysis will be by intention to treat. The analysis will compare the proportions of patients testing positive for and the levels or titres of antibodies to HNPs or leiomodin at baseline and at 24 months in both arms. Both crude (unadjusted) and adjusted effect estimates will be computed. The chi square test will be used to compare proportions of children with the different antibodies in the two arms; the Students t-test will be used for means of normally distributed data and the Mann-Whitney U test for skewed data. We will also determine the mean change or reduction in the levels or titres of the antibodies and inflammatory markers with the intervention. Time to event (e.g. to seizure resolution) will be measured from the date of randomisation using Kaplan Meyer Survival analysis and by Cox regression analysis. For the cognitive tests, in addition to classification as impaired or not (in comparison to norms determined from unaffected sibling controls in the concurrent case control study), we will also measure mean improvements in scores. The rates determined will be adjusted for age, HIV infection, weight for height z scores and corrected for multiple testing. We will examine safety (serious adverse events and adverse events) and assess compliance and the factors for poor compliance.

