### Interim analyses and criteria for termination of the trial

An interim analysis is planned for when a total of 132 participants have completed the 24-month assessment. This number will be sufficient to demonstrate a 50% reduction in the proportion of participants testing positive for antibodies to HNPs at 24 months compared to baseline at β = 0.80 and α = 0.05. This information will be reviewed by an independent Data and Safety Monitoring Committee (composed of an experienced epidemiologist who will chair the committee, a paediatric neurologist and a general paediatrician) which may recommend stopping the trial on safety rules or efficacy reasons. The Peto-Haybittle rule will be used to stop the trial for efficacy reasons: i.e. to consider stopping the trial early because of efficacy, a *p-value* < 0.001 should be achieved at the interim analysis. Accordingly, the early stopping rules will be: (1) proof beyond reasonable doubt of a difference in primary outcome between the study and control groups and (2) evidence that would substantially alter the choice of treatment for patients. Otherwise, the overall significance level of the final analysis will be *p* < 0.05. *However, in order not to miss an early but clinically relevant improvement in secondary outcomes and in particular, seizure control, Makerere University School of Medicine Research and Ethics Committee recommended that the first interim analysis should be conducted when 132 participants complete the 12-month assessment. If significant differences fulfilling the Peto-Haybittle rule are observed at this stage, the trial may be stopped.*

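### The only adjustment set named leaves out baseline seizure burden, so adjusted analyses of the secondary seizure outcomes may give up a little power

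*Protocol article*

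**What the plan says.** Under Statistical analysis the article commits to two kinds of estimate, "Both crude (unadjusted) and adjusted effect estimates will be computed", and gives a single covariate list: "The rates determined will be adjusted for age, HIV infection, weight for height z scores and corrected for multiple testing". No other section adds a covariate.

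The seizure outcomes are these:
- Secondary efficacy outcomes lists the proportion achieving "seizure freedom (≥1 month without head nodding or convulsive seizures" at 24 months.
- Statistical analysis adds a Kaplan-Meier and Cox analysis: "Time to event (e.g. to seizure resolution) will be measured from the date of randomisation".
- The interim section brings the first look forward to 12 months, "in order not to miss an early but clinically relevant improvement in secondary outcomes and in particular, seizure control".

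The Inpatient assessment section records "the burden and types of seizures" at baseline, and randomisation follows only once those assessments are complete. Allocation is 1:1 and "stratified by skin snip test results", so seizure burden is not balanced by design either.

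**The concern.** A baseline measure of the outcome is usually the first candidate for adjustment. Here the three named covariates are general patient characteristics, and none is the baseline form of a seizure outcome. Several other secondary outcomes use their baseline value through a mean change. The seizure outcomes, as described, use no baseline seizure information.

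The trial population may well be mixed in this respect. Eligibility is "The inclusion criteria will be patients with confirmed nodding syndrome as defined by the WHO [25] and aged 8 years or older", with no minimum current seizure frequency. The randomisation criteria refer to valproate dosing for patients who still have at least one tonic-clonic seizure a month, which implies that others do not.

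At stake is some power in the secondary seizure comparisons, on a clinical outcome that the interim section singles out.

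**Working it through.** **Inputs from the protocol article.** 230 participants, 1:1, 10% loss, 5% significance and 80% power for 50% v 30% antibody positivity (Sample size); 132 participants and p < 0.001 at the interim look (Interim analyses).

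**Inputs assumed.** Seizure-freedom rates, the distribution of baseline burden and its prognostic strength. The article gives none of these, so ranges are shown.

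**1. The plan's own figure.** With pooled rate 0.40 and a two-sided test, n = (1.96 × √(2 × 0.4 × 0.6) + 0.842 × √(0.5 × 0.5 + 0.3 × 0.7))² / 0.2² ≈ 93 per arm. The continuity correction, (n/4) × (1 + √(1 + 4/(n × 0.2)))², raises this to 103. Then 103 / 0.9 = 114.4, rounded up to 115 per arm, or 230 in total. The stated size is reproduced, and nothing here changes it. About 103 per arm are evaluable.

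**2. Power for seizure freedom, three covariates v four.** Logistic simulation, 103 per arm, 10,000 runs per cell. Both models contain age, HIV and weight-for-height; the second adds log(monthly count + 1). Counts are assumed overdispersed, with about 20% zeros.

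| Odds ratio per SD of burden | 30% v 50% | 50% v 65% | 20% v 35% | Gain (points) |
|---|---|---|---|---|
| 1.0 (useless) | 83.8 → 83.6 | 59.0 → 59.1 | 66.9 → 67.0 | −0.2 to 0.1 |
| 0.8 | 83.3 → 83.5 | 58.3 → 59.0 | 67.6 → 68.0 | 0.2 to 0.7 |
| 0.67 | 83.7 → 85.0 | 57.9 → 59.5 | 67.2 → 68.5 | 1.3 to 1.6 |
| 0.5 | 84.2 → 87.8 | 59.3 → 63.8 | 67.7 → 71.4 | 3.6 to 4.5 |
| 0.33 | 83.8 → 90.2 | 59.2 → 68.6 | 67.3 → 74.7 | 6.4 to 9.4 |

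The simulation standard error of each difference is 0.1 to 0.4 point. Type I error is 4.8–5.7% with three covariates and 4.9–5.2% with four. Ordered categories (0, 1–3, 4–12, 13+ a month) give similar gains: 0.2–0.7, 1.2–1.3, 2.8–4.2 and 6.8–9.0 points at 0.8, 0.67, 0.5 and 0.33.

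**3. What kind of gain it is.** A second simulation (3,000 runs, 103 per arm, 30% v 50%) compared no covariate with one standardised baseline covariate.

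| Odds ratio per SD | Power | SE of log odds ratio | Variance of standardised risk difference, ratio to unadjusted |
|---|---|---|---|
| 1.0 | 85.5 → 85.0 | 0.294 → 0.295 | 1.00 |
| 1.6 | 84.2 → 86.1 | 0.294 → 0.305 | 0.94 |
| 2.7 | 84.0 → 89.7 | 0.294 → 0.329 | 0.83 |
| 4.5 | 84.1 → 93.6 | 0.294 → 0.363 | 0.74 |

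Power rises although the conditional standard error also rises, because the conditional odds ratio lies further from 1. Precision improves only for the standardised (marginal) risk difference. The useless covariate costs 85.5 − 85.0 = 0.5 point, the largest cost seen.

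**4. Time to seizure resolution.** Cox simulation (2,000 runs, treatment hazard ratio 1.5 or 1.7, 40% or 60% events under control): gain 1.2–1.8 points at a hazard ratio of 0.8 per SD and 2.9–4.9 at 0.67. At 0.5 it is 9–15, but that assumes a strong covariate and is not relied on.

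**5. The 12-month look.** 132 / 2 = 66 per arm, p < 0.001, 30% v 50% seizure-free. Power goes from 15.6 to 16.4, 15.5 to 17.5 and 15.9 to 20.8 at odds ratios of 0.67, 0.5 and 0.33 per SD. This applies only if that test is adjusted.

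**The case against.** The strongest reply is that nothing is wrong. The analysis is valid, and a condensed article may leave outcome-specific models to a fuller document. No logistic model is named anywhere, so the comparator in the working is partly a construction. The adjustment sentence speaks of rates without saying which outcomes it covers, and nothing says whether the crude or the adjusted estimate carries the inference. Prognostic strength may also be low: patients are moved to valproate, started on it or dose-optimised around the baseline measurement, and seizure freedom is judged 24 months later.

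All of this stands as a limit on the size of the point. It does not remove it, because the article names its covariates instead of referring to a set to be specified later, and a named list can be judged.

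A reader might infer three stronger things, none of which the article supports:
- That the seizure comparisons are biased. Allocation is randomised and double-blind, so they are not.
- That adjustment would shrink the standard error of the odds or hazard ratio. In the logistic check the conditional standard error rises.
- That the omission weakens the 12-month look. The interim section does not say that test is adjusted, and power there stays at about 21% or below in every case tried.

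**Conclusion.** The point holds as a minor efficiency matter in secondary outcomes. Adding baseline burden gains about 0 to 4 points of power for seizure freedom if burden is weakly to moderately prognostic (odds ratio 0.8 to 0.5 per SD; 4.5 at most in the scenarios tried). Gains of 6 points or more need a strongly prognostic covariate. These figures rest on assumed event rates, an assumed burden distribution and the premise that the adjusted analysis is the one used for inference.

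A related gap is that entry does not require current seizures. A patient with no seizures in the month before randomisation would already satisfy the one-month definition of seizure freedom. If resolution is defined the same way, time to resolution has no clear meaning for that patient, and a covariate does not solve this.

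**What to change.** - In any adjusted analysis of seizure freedom, and in the Cox model for time to seizure resolution, add pre-randomisation seizure burden to age, HIV infection and weight-for-height.
- Match its form to what is recorded: log(monthly frequency + 1) if there is a count, ordered categories if burden is graded. The article does not say which.
- Set the time window and the missing-value rule before unblinding. The window matters because valproate is changed before randomisation. Do not adjust for doses given after randomisation.
- If precision is the aim, report a standardised risk difference for seizure freedom. Keep the crude estimates as planned.
- State how patients already seizure-free at entry enter the time-to-resolution analysis.
- Say whether the 12-month seizure test is adjusted.

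The cost is a short addition to the analysis text and one or a few degrees of freedom, worth about 0.5 point of power or less if the covariate proves useless. Burden is already part of the baseline assessment, and the sample size does not change.

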### Interim analyses and criteria for termination of the trial

An interim analysis is planned for when a total of 132 participants have completed the 24-month assessment. This number will be sufficient to demonstrate a 50% reduction in the proportion of participants testing positive for antibodies to HNPs at 24 months compared to baseline at β = 0.80 and α = 0.05. This information will be reviewed by an independent Data and Safety Monitoring Committee (composed of an experienced epidemiologist who will chair the committee, a paediatric neurologist and a general paediatrician) which may recommend stopping the trial on safety rules or efficacy reasons. The Peto-Haybittle rule will be used to stop the trial for efficacy reasons: i.e. to consider stopping the trial early because of efficacy, a *p-value* < 0.001 should be achieved at the interim analysis. Accordingly, the early stopping rules will be: (1) proof beyond reasonable doubt of a difference in primary outcome between the study and control groups and (2) evidence that would substantially alter the choice of treatment for patients. Otherwise, the overall significance level of the final analysis will be *p* < 0.05. *However, in order not to miss an early but clinically relevant improvement in secondary outcomes and in particular, seizure control, Makerere University School of Medicine Research and Ethics Committee recommended that the first interim analysis should be conducted when 132 participants complete the 12-month assessment. If significant differences fulfilling the Peto-Haybittle rule are observed at this stage, the trial may be stopped.*

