### Sample size

From our pilot studies, ~ 50% of patients with prevalent nodding syndrome had antibodies to a HNPs and ~ 60% to leiomodin [2, 22]. We hypothesise that among patients with new onset nodding syndrome (symptoms < 12 months), six weeks’ therapy with doxycycline will cause a 50% reduction in the proportion of patients with and the levels or titres of antibodies to HNPs (a reduction from 50 to 25% compared to placebo) at 24 months. In Uganda, however, there has been no incident cases of nodding syndrome since 2014. It is anticipated that the intervention may not be as efficacious in patients with established symptoms (i.e. patients with symptoms ≥12 months) and the effect on antibodies would be smaller (an anticipated 40% reduction from 50 to 30%). To demonstrate this effect at 80% power and 5% level of significance and allowing for 10% losses to follow up, we will need to recruit a total of 230 patients with established symptoms (115 in either arm).

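### The reason given for the 132-participant interim look (50% reduction from baseline, α 0.05) does not match the test applied there (between arms, p < 0.001, 50% v 30% planned), so it overstates what the look can show

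*Protocol article*

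**What the plan says.** The interim section of the protocol article sets the timing of the look: "An interim analysis is planned for when a total of 132 participants have completed the 24-month assessment". It justifies that number as "sufficient to demonstrate a 50% reduction in the proportion of participants testing positive for antibodies to HNPs at 24 months compared to baseline", with error rates printed as "β = 0.80 and α = 0.05".

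The same section then gives the rule that will be applied. Under Peto-Haybittle, a p-value "< 0.001 should be achieved at the interim analysis" before stopping for efficacy is considered, and the first criterion is "proof beyond reasonable doubt of a difference in primary outcome between the study and control groups". The final analysis keeps p < 0.05.

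The Sample size section gives two effect assumptions:

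- The 50% reduction is expected "among patients with new onset nodding syndrome (symptoms < 12 months" and is written as "a reduction from 50 to 25% compared to placebo".
- The section then says that Uganda has had no incident cases since 2014. It sizes the trial at 230 patients with established symptoms (115 per arm), on "an anticipated 40% reduction from 50 to 30" percent, with 80% power, 5% significance and 10% loss to follow-up.

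**The concern.** The sentence that justifies the look and the rule that governs it differ in three respects.

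- **Threshold:** α = 0.05 in the justification, p < 0.001 in the rule.
- **Effect and population:** a halving, which the protocol expects in new-onset patients, against the 40% reduction it plans for the patients it will recruit.
- **Comparison:** change from baseline in the justification, doxycycline against placebo in the rule.

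In addition, β = 0.80 read literally means 20% power; 0.80 is plainly meant as power.

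The independent committee reviews this look and may recommend stopping. A committee told that 132 is enough to demonstrate the effect could take a non-significant look as evidence against the drug. It could also give weight to a fall from baseline, which mixes any drug effect with natural decline and regression to the mean. The placebo arm is there to separate these.

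**Working it through.** **Inputs.** From the Sample size section: 50% positive on placebo; 25% (new-onset) or 30% (established) on doxycycline; 80% power; 5% level; 10% loss. From the randomisation section: 1:1 allocation. From the Statistical analysis section: chi-square test between arms. From the interim section: 132 completers and p < 0.001. Assumptions: an even split (66 per arm) and two-sided tests, since the article does not state sidedness. Two-sided 0.05 is what reproduces 132.

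**Step 1: reproduce the protocol's numbers.** With p̄ the mean of p₁ and p₂, and d = p₁ − p₂:

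n = [1.960·√(2p̄(1−p̄)) + 0.842·√(p₁(1−p₁)+p₂(1−p₂))]² / d²

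n_cc = (n/4)·[1 + √(1 + 4/(n·d))]²

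- 50% v 25%: p̄ = 0.375, n = (1.960×0.6847 + 0.842×0.6614)²/0.25² = 57.7; n_cc = 65.4, so 66 per arm and **132 in total**, the stated interim size. Without the continuity correction it would be 58 per arm, 116 in total.
- 50% v 30%: p̄ = 0.40, n = 93.0; n_cc = 102.8, so 103 per arm; 103/0.9 = 114.4, so 115 per arm and **230 in total**, the stated final size.

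Both sizes match exactly as two-arm calculations. The 132 is therefore the new-onset scenario, arm against arm, at two-sided 0.05.

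**Step 2: power of the test actually applied, 66 per arm.** Normal approximation: power = Φ{[d√66 − z·√(2p̄(1−p̄))] / √(p₁(1−p₁)+p₂(1−p₂))}, with z = 3.291 for two-sided 0.001.

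- 50% v 25%: (2.031 − 2.253)/0.6614 = −0.335, power 36.9%.
- 50% v 30%: (1.625 − 2.280)/0.6782 = −0.966, power 16.7%.

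Exact enumeration over both binomials gives:

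| Contrast | Two-sided level | Uncorrected chi-square | Continuity-corrected |
|---|---|---|---|
| 50% v 25% | 0.05 | 86% | 81% |
| 50% v 25% | 0.001 | 37% | 31% |
| 50% v 30% | 0.05 | 65% | 58% |
| 50% v 30% | 0.001 | **17%** | **13%** |

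Fisher's exact test gives 13% in the last row. If the 0.001 were one-sided, the normal approximation for 50% v 30% would be about 22%.

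**Step 3: what crossing requires.** Take 33/66 positive on placebo.

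- 14/66 on doxycycline gives z = 3.45 uncorrected, which crosses 3.29, but z = 3.27 corrected, which does not.
- 15/66 gives z = 3.26 uncorrected, which does not cross.
- 13/66 gives z = 3.47 corrected, which crosses.

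The requirement is therefore 14/66 (21%) or fewer uncorrected, or 13/66 (20%) or fewer corrected. The planned doxycycline rate is 30%.

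**Step 4: size needed for the claim at this boundary.** For 80% power at two-sided 0.001 with 50% v 30%, the Step 1 formula with 3.291 in place of 1.960 gives 203.1, so 204 per arm (uncorrected). The whole trial has 115 per arm.

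**The case against.** The strongest defence is that nothing has been miscalculated. The figure of 132 is correct for its inputs, the sentence is conditional on a 50% reduction, and the article does not claim 80% power at p < 0.001. Low power at an early look is what a Haybittle-Peto boundary is designed to give, and the boundary is stated openly. There is no futility rule, so failing to cross triggers nothing. Acting on p < 0.05 or on a within-arm fall would breach the article's own rule. The Sample size section and the Discussion both say that a smaller effect is expected in established patients. The baseline wording and the β label look like slips, since the same section's stopping criterion is between arms.

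Most of this stands, and it limits the point. A reader might infer that the interim size is an arithmetic error, that the stopping rule is invalid, or that the trial is underpowered. The documents support none of these: 132 and 230 both reproduce, a p < 0.001 look has negligible effect on the final 0.05 test, and final power rests on the 230.

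The defence does not rescue the justification. It presents as sufficient a number derived at a threshold the look does not use and for a population the trial will not recruit, and it describes a comparison the rule does not make. The Statistical analysis section also mentions comparing proportions at baseline and 24 months in both arms, so the baseline wording is not self-evidently a slip to every reader.

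**Conclusion.** The point holds as an internal inconsistency of moderate severity. Under the protocol's own boundary and planned effect, the 132-participant look has power of about 13–17%, and about 31–37% even if the new-onset effect applied. If the planned effect is real, the look will fail to cross about 83–87% of the time, so not crossing says little about whether the drug works. A misreading by the committee is a possibility; nothing in the article's rules would lead to it directly.

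The figures assume 66 per arm, a 50% placebo rate and a two-sided 0.001. Each range runs from the continuity-corrected to the uncorrected chi-square. They apply only to the 24-month antibody look. The added look at 12 months cannot borrow them, because the follow-up section schedules only clinical assessments at that visit.

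**What to change.** Replace the justification sentence with:

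> The look at 132 completers of the 24-month assessment (about 66 per arm) compares doxycycline with placebo. At two-sided p < 0.001 its power is about 31–37% for 50% v 25% and about 13–17% for the planned 50% v 30% (continuity-corrected to uncorrected chi-square). Not crossing is not evidence of no effect.

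This removes the comparison with baseline. Wherever the original design inputs behind 132 are still cited, change β = 0.80 to power = 0.80. If a crossing example is given to the committee, state which test it uses: with 33/66 positive on placebo, 14/66 or fewer uncorrected, or 13/66 or fewer continuity-corrected. State that the figures do not cover the 12-month look.

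The cost is wording only. The boundary, the timing of the 24-month look, the final significance level and the sample size stay as they are. The stated property of the look becomes less favourable.
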